#### Non-specific acupoints group

The acupoints used in this group consist of six fixed acupoints (Table 2): *Shuifen* (RN9), *Liangmen* (ST21), *Yinjiao* (CV7), *Tiaokou* (ST38), *Yinshi* (ST33), *Lougu* (SP7), *Yinbao* (LR9). The rest of the operation is the same as that of the SA group.

**Table 2 Tab2:** Locations of acupoints for NSA group

	Acupoint	Location
Fixed acupoints of NSA group	*Shuifen* (RN9)	On the anterior midline of the upper abdomen, 1 cun^a^ superior to the navel
	*Liangmen* (ST21)	On the anterior midline of the upper abdomen, 1 cun superior to the navel, 2 cun beside the anterior midline
	*Yinjiao* (CV7)	On the anterior midline of the abdomen, 1 cun inferior to the navel
	*Tiaokou* (ST38)	On the anterolateral aspect of the leg, 8 cun inferior to the ST35, and on the line between ST35 and ST41
	*Yinshi* (ST33)	On the anterior aspect of the thigh, 3 cun superior to basis patellae, and on the line between anterior superior iliac spine and basis patellae
	*Lougu* (SP7)	On the anteromedial aspect of the leg and the tibial rear, on the line between medial malleolus and SP9, and 6 cun superior to medial malleolus

^a^1 cun (≈20 mm) is defined as the width of the interphalangeal joint of the patient’s thumb

#### Non-acupoints group

Patients in this group will receive sham acupuncture with blunt-tipped placebo needles on non-acupoints. Five non-acupoints will be selected which are away from meridians or conventional acupoints. The use of blunt-tipped placebo needles will provide patients with the feeling of acupuncture but with no skin penetration and needle manipulation for *de qi*. The non-acupoints are shown in Table 3.

**Table 3 Tab3:** Locations of acupoints for NA group

NA	Location
NA1	On the abdomen, 2 cun^a^ superior to anterior superior iliac spine, between the gallbladder meridian and the spleen meridian
NA2	On the abdomen, 2 cun inferior to navel, 1 cun beside the anterior midline, between the kidney meridian and the stomach meridian
NA3	On the lateral aspect of the leg, 3 cun inferior to GB34, between gallbladder meridian and bladder meridian
NA4	On the leg, 2 cun superior to the medial malleolus, in the middle of the medial tibia, between the liver meridian and the spleen meridian
NA5	On the leg, the midpoint of the line between GB40 and ST41, between the gallbladder meridian and the stomach meridian

^a^1 cun (≈20 mm) is defined as the width of the interphalangeal joint of the patient’s thumb

### Outcomes

#### Primary outcome

In this trial, the response rate defined as the percentage of patients whose average value of worst abdominal pain is 30% better and the days of loose stool is 50% less than the baseline. The primary outcome is the response rate of week 4 after randomization. Patients will be asked to record daily IBS symptoms, including worst abdominal pain and stool type through Bristol Stool Scale. The score of worst abdominal pain in the preceding 24 h will be evaluated by visual analog scale (VAS), and the average value of worst abdominal pain will be calculated weekly.

#### Secondary outcomes

##### The response rates at other time points

The response rate will also be measured at weeks 1, 2, 3, 8, and 12 after randomization.

##### IBS Symptom Severity Scale (IBS-SSS)

The IBS-SSS contains five questions that are rated on VAS (0–100): severity of abdominal pain, frequency of abdominal pain, severity of abdominal distension, degree of dissatisfaction with defecation habits, and interference with the quality of life. The above five aspects account for an equal proportion in the IBS-SSS with a score range of 0–500. A score below 175 indicates that the mild IBS syndrome, a score between 175 and 300, represents the moderate IBS syndrome and a score higher than 300 represents the severe IBS syndrome [23]. IBS-SSS will be used at weeks 2, 4, 8, and 12 after randomization.

##### Patient Health Questionnaire-9 depression scale (PHQ-9)

PHQ-9 scores range from 0 to 27, by which depression is defined as mild (5–9), moderate (10–14), moderate (15–19), or severe (more than 20) [24]. PHQ-9 will be used at weeks 2, 4, 8, and 12 after randomization.

##### IBS-Quality of Life scale (IBS-QOL)

IBS-QOL, which consists of 34 items, will be used to assess the extent to which the quality of life of patients with IBS is disturbed. Each item will be evaluated with a 5-point Likert scale, and the cumulative total score of all items will be linearly converted into a 100-point scale. The higher score indicates the improvement in quality of life is more obvious [25]. IBS-QOL will be used at weeks 2, 4, 8, and 12 after randomization.

##### IBS Adequate Relief (IBS-AR)

IBS-AR will be used to confirm whether the IBS symptoms of trial patients have been adequately relieved. This type of outcome has been shown to be associated with the improvement of individual symptoms [26] and has been extensively used to evaluate efficacy in IBS clinical trials [27, 28]. The responder is defined as the patient who answered the question in the affirmative. IBS-AR will be used at weeks 1, 2, 3, 4, 8, and 12 after randomization.

##### Abdominal Pain Score

Patients will be asked to rate their worst abdominal pain in the past 24 h. The pain will be recorded on VAS (0–10), where 0 corresponds to no pain and 10 corresponds to worst imaginable pain. The score will be measured at weeks 1, 2, 3, 4, 8, and 12 after randomization.

##### Abdominal Bloating Score

Patients will be asked to rate their worst abdominal bloating in the past 24 h. The bloating will be recorded on VAS (0–10), where 0 corresponds to no bloating and 10 corresponds to worst imaginable bloating. The score will be measured at weeks 1, 2, 3, 4, 8, and 12 after randomization.

##### Bristol Stool Score (BBS)

Patients will be asked to rate the BBS of the past 24 h. The score is based on a 1 to 7 scale where 1 corresponds to a hard stool and 7 corresponds to watery diarrhea. And the frequency of each score will be also recorded. The BBS will be measured at weeks 1, 2, 3, 4, 8, and 12 after randomization.

##### Blinding assessment

To test whether blinding is successful, all patients will be asked to guess which kind of acupuncture they received at week 4 after randomization.

##### Credibility and expectancy

Credibility and expectancy will be evaluated using the Credibility/Expectancy Questionnaire within 5 min after the first treatment.

The schedule of enrollment, intervention, and assessments is shown in Fig. 2.

**Fig. 2 Fig2:**
[figure not shown]
Schedule of enrollment, intervention, and assessments

### Sample size

This pilot study aimed to assess the effectiveness of different acupuncture intervention for IBS and determine the feasibility of a further large clinical trial. The minimum sample size for exploratory trials is 20–30 per group according to Provisions for Drug Registration in China. We selected the maximum of 30 patients, and the sample size of 90 patients was determined. The results of this study will facilitate the calculation of an appropriate sample size for further randomized clinical trials.

### Randomization

#### Sequence generation

Patients need to finish their defecation diary in the last 2 weeks before randomization. After screening, patients will be randomly assigned to the SA group, NSA group, and NA group according to the ratio of 1:1:1. The block randomization will be used in the trial. An independent statistician who is not involved in the implementation or statistical analysis of this trial will generate the blocked randomization sequence by using the software SAS 9.3.

#### Allocation concealment mechanism

The randomization sequence will be stored by the special randomization sequence manager and will not be available to other participating investigators. The allocation schedule will be using a telephone randomization procedure. The clinical research coordinators will be responsible for requesting randomization.

### Implementation

The blocked randomization sequence will be generated by an independent statistician. The recruiter is responsible for registration. The acupuncturist will assign participants to related interventions.

### Blinding

Patients, outcome assessor and statistician will be blinded to the assignments. During the treatment, the adhesive pads will be glued to the corresponding sterilized acupoints in order to make it impossible for patients to distinguish between the use of single-use sterile needles and blunt-tipped placebo needles. When two or more patients are treated at the same time, they will be screened or assigned to separate treatment rooms in order to refraining from communication. Interventions of patients will not be revealed until the statistical analysis is completed.

Every effort should be made to preserve the blind. Should a medical emergency arise that requires identification of the study acupuncture administered in order to manage the acute situation of the patient, the blind can be broken. The investigator should make every effort to contact the clinical gastroenterologist to discuss the use of rescue medication or other necessary treatments. If blinding is broken ahead of time, it is necessary to record the time, reasons, and executive personnel who break the blindness in advance and notify the inspector as soon as possible. And related patients should not continue to participate in the trial, and the trial data cannot be used for efficacy evaluation analysis, but should still be included in the safety analysis data set. Other available treatments should also be provided to related patients.

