### Interventions

Before acupuncture treatment, licensed acupuncturists with at least 3 years of acupuncture experience will be trained in how to locate acupoints and non-acupoints, puncture and manipulate needles. All acupoints are localized according to the WHO Standard. Single-use sterile needles (0.30 mm in diameter and 30 mm in length or 0.30 mm in diameter and 25 mm in length; Hwato, Suzhou, China) will be used in the SA group and NSA group. To help maximize blinding of patients in the NA group, a blunt-tipped placebo needle will be used (similar to the Streitberger design [21]) which can provide patient-blinding effects with a similar appearance to conventional needles but no skin penetration [22]. And adhesive pads will be used in each group. Each patient will be scheduled to undergo 12 sessions of treatment, with each acupuncture lasting 30 min for 4 weeks (three sessions per week, every other day ideally). During the trial, patients will not be allowed to use other therapies or medications that have a therapeutic effect on IBS, such as traditional Chinese medicine (TCM) or proprietary Chinese medicine, antidiarrheal, antispasmodic, intestinal antibiotics, probiotics, and so on. Loperamide (Imodium, Xian Janssen Pharmaceutical Ltd., China) will be used as rescue medication under the guidance of gastroenterologists whenever necessary. The medication status and other non-irritable bowel syndrome drug applications of patients will be strictly recorded during the trial.

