### Analytical methods

In this study, statisticians who blind to the group assignment will perform analyses using SPSS 22.0 statistical software. Continuous data will be represented by mean ± standard deviation (M ± SD) or median combined with interquartile range, whereas categorical data will be represented by frequency, constituent ratio, and percentage. Student’s *t* test or Wilcoxon rank-sum test will be used for the comparison of continuous variables, and chi-square test or Wilcoxon rank-sum test will be used for the comparison of categorical variables. *P* < 0.05 is considered to indicate statistical significance. Intention-to-treat (ITT) set will be used in all efficacy analysis, which will consist of all patients who have been randomized into groups, and the missing outcome data will be complemented using last observation carried forward (LOCF) or multiple imputation.

For the primary outcome, covariate analysis will be conducted applying a logistic regression model that includes baseline covariates for both pain score and stool consistency. A per-protocol analysis will be used for primary outcome as sensitivity analysis covering patients who complete ≥ 10 sessions and have no major protocol violations (taking other drugs during the trial, etc.).

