### Data management

Before recruiting patients, the case report form (CRF) will be established to input and store data. The outcome evaluator will be responsible for recording the corresponding results of the outcome indicators in the appropriate location in the CRF. While the trial is completed, the data management team will lock the database and the researchers can no longer modify the data. The patients’ relevant information, name, ID card number, and telephone number, will be kept anonymously. Some patients participate in the trial blindly and do not reasonably judge whether their own conditions can complete the content of the test, which will increase the drop-off rate. We have trained researchers to establish a good communication relationship with patients to ensure that patients have a more comprehensive understanding and cooperation of the trial before randomization. For patients who discontinue or deviate from intervention protocols, we will try to get as much trial data as possible by telephone, if the patient is willing to provide it.

Documents of patients’ information will be preserved for at least 5 years after publication. If readers and reviewers have any questions, in the meantime, they can contact the corresponding author for access to the original data. In addition, quality controllers will be independently established in each center to review and interpret the data of trial. They will review the progress of the trial, independently of the investigators, and decide whether the trial needs to be terminated early solely on the basis of adverse events.

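### The rule barring efficacy data from patients whose blind is broken contradicts the rule that all randomized patients enter every efficacy analysis

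*Protocol article*

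**What the plan says.** Two sections of the protocol article set the efficacy population.

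- **Blinding.** The blind may be broken in a defined situation: "Should a medical emergency arise that requires identification of the study acupuncture administered in order to manage the acute situation of the patient". If it is broken early, the time, the reasons and the person responsible are recorded. Then: "And related patients should not continue to participate in the trial, and the trial data cannot be used for efficacy evaluation analysis". The sentence next turns to safety, where the rule differs: "but should still be included in the safety analysis data set".
- **Analytical methods.** "Intention-to-treat (ITT) set will be used in all efficacy analysis, which will consist of all patients who have been randomized into groups". For gaps, "the missing outcome data will be complemented using last observation carried forward (LOCF) or multiple imputation". The only smaller efficacy set named is a per-protocol sensitivity analysis of the primary outcome, for patients with at least 10 sessions and no major violation. Unblinding is not mentioned there.

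A third section bears on the point. **Data management** says, subject to the patient's agreement: "For patients who discontinue or deviate from intervention protocols, we will try to get as much trial data as possible by telephone".

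**The concern.** A randomized patient whose blind is broken is in every efficacy analysis under one section and in none under the other. Whoever analyses the trial must break one written rule. If the choice is still open when results are known, it can be made in their light.

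The exclusion rule is the weaker of the two, for three reasons.

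- It selects on something that happens after randomization. An emergency may be related to how the patient is doing, or to the arm: the SA and NSA groups receive penetrating needles with manipulation, the NA group blunt needles that do not pierce the skin. Randomization no longer protects a comparison that drops such patients.
- It covers all of the patient's data, not only what follows the code break. The primary outcome is at week 4 and follow-up runs to week 12, so a patient unblinded in week 10 would lose a week 4 result reported while blinded.
- The analysis would carry the intention-to-treat label without being one.

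The pilot's response rates are also meant to help size a later trial, so the denominator should be unambiguous.

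**Working it through.** **1. Planned denominator.** Sample size section: 30 per group in three groups. 3 × 30 = 90, which reproduces the stated total. The section uses a per-group convention and gives no response rate or power, so there is no power figure to recompute.

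**2. The two rules applied to one patient.** Take a randomized patient whose blind is broken early.

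| Question | Blinding | Analytical methods |
|---|---|---|
| In the efficacy analysis? | No | Yes, in all of them |
| Outcomes before the code break | Not usable for efficacy | Used |
| Outcomes missing afterwards | Not applicable | Imputed |
| Efficacy denominator | 90 minus the number unblinded | 90 |

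The rules agree only if nobody is unblinded. The Blinding section does not limit its exclusion to the per-protocol set. It contrasts efficacy analysis as a whole with the safety set.

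**3. How much a few exclusions could move a rate.** The document gives neither an unblinding rate nor an expected response rate, so the inputs are assumptions: 10 responders of 30 in one arm, k patients removed from that arm only, and all k non-responders. The rate after exclusion is 10/(30 − k).

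- k = 0: 10/30 = 33.3%
- k = 1: 10/29 = 34.5% (+1.1 points)
- k = 2: 10/28 = 35.7% (+2.4 points)
- k = 3: 10/27 = 37.0% (+3.7 points)

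With 9 to 15 responders of 30 (30% to 50%), the rise is 1.0 to 1.7 points for k = 1, 2.1 to 3.6 for k = 2 and 3.3 to 5.6 for k = 3.

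**4. The sign depends on who is removed.** If the excluded patients were responders, the rate would be (10 − k)/(30 − k): 9/29 = 31.0%, 8/28 = 28.6%, 7/27 = 25.9%. The same rule then lowers the arm's rate.

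**5. Effect on a two-arm test, same worst case.** This is an exact binomial enumeration: 30 per arm, equal true rates, chi-square without continuity correction, 0.05 level taken as two-sided (the document does not state sidedness), and k non-responders dropped from one arm. Over true rates of 30% to 50%, the type I error is:

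- k = 0: 0.049 to 0.052
- k = 1: 0.054 to 0.057
- k = 2: 0.055 to 0.063
- k = 3: 0.069 to 0.088

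These are upper illustrations, not forecasts.

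**The case against.** **A specific rule may override a general one.** The Blinding sentence could be meant as an exception to the all-randomized rule. The text does not say so, and the general rule is worded without exception. A separate analysis plan could not settle it without departing from one of the two sections.

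**Code breaks may be rare or absent.** The Discussion accepts that acupuncturists cannot be blinded, so treating staff already know the allocation and a formal code break may seldom be needed. The trial is also an exploratory pilot. This stands. It limits the expected harm and the urgency, but does not reconcile the sections.

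**The exclusion need not favour any arm.** A reader might infer that unblinding follows bad symptoms, so that the rule removes non-responders and inflates response. There is some support: the same paragraph says "The investigator should make every effort to contact the clinical gastroenterologist to discuss the use of rescue medication or other necessary treatments", and under Interventions loperamide "will be used as rescue medication under the guidance of gastroenterologists whenever necessary". The documents do not carry the inference further. The trigger is any medical emergency, the exclusion applies to any early unblinding, and nothing says that rescue use requires a code break. A reaction to needling says little about pain or stool response. The defensible statement is that the event may be related to outcome or arm, with unknown direction.

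**The telephone follow-up is not a direct conflict.** Data management speaks of patients who discontinue or deviate and does not mention code breaks. The Blinding section also keeps these patients' data for safety. This stands: the Blinding rule would bar the efficacy use of such data where the patient left after a code break, and no more.

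**Scores reported after a code break may be biased.** The outcomes are patient-reported, and a patient who knows the allocation may answer differently. This is a real cost of keeping such data. It does not justify discarding outcomes recorded before the break.

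**Conclusion.** The contradiction is certain from the text: the Blinding and Analytical methods sections define incompatible efficacy populations, and nothing else in the protocol reconciles them. It should be corrected, but it is not shown to threaten the main result.

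If the Blinding rule were followed, the analysis would exclude patients on a post-randomization event, lose outcomes recorded while they were blinded, and not be intention-to-treat as labelled. The bias cannot be signed or sized from the document. The shift from 33.3% to at most 37.0% assumes 10 responders of 30, up to three code breaks, all in one arm and all in non-responders. With no code breaks the effect is nil.

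**What to change.** In the Blinding section, delete the clause barring these patients' data from efficacy analysis. In its place state that:

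- patients whose blind is broken stay in the intention-to-treat set in their randomized arm;
- all efficacy data actually recorded for them are used, with the time of the code break flagged;
- what is missing follows the trial's missing-data rule (the protocol names two methods, and these patients follow whichever is adopted for everyone);
- any exclusion for unblinding applies only to the per-protocol sensitivity analysis, whose definition should then name it.

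The cost is about one sentence, repeated in the analysis plan if there is one. No further patients, visits or data are needed: the protocol already has the time of a code break recorded, and the change uses only what was collected. The small downside is possible influence of known allocation on later self-reported scores, which the per-protocol analysis can check. Whether such patients stop trial treatment is a clinical matter and is not addressed here.

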### Analytical methods

In this study, statisticians who blind to the group assignment will perform analyses using SPSS 22.0 statistical software. Continuous data will be represented by mean ± standard deviation (M ± SD) or median combined with interquartile range, whereas categorical data will be represented by frequency, constituent ratio, and percentage. Student’s *t* test or Wilcoxon rank-sum test will be used for the comparison of continuous variables, and chi-square test or Wilcoxon rank-sum test will be used for the comparison of categorical variables. *P* < 0.05 is considered to indicate statistical significance. Intention-to-treat (ITT) set will be used in all efficacy analysis, which will consist of all patients who have been randomized into groups, and the missing outcome data will be complemented using last observation carried forward (LOCF) or multiple imputation.

For the primary outcome, covariate analysis will be conducted applying a logistic regression model that includes baseline covariates for both pain score and stool consistency. A per-protocol analysis will be used for primary outcome as sensitivity analysis covering patients who complete ≥ 10 sessions and have no major protocol violations (taking other drugs during the trial, etc.).

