## Methods

### Trial design

This is a study protocol for a randomized, multicenter, clinical trial. Patients with IBS will be randomly assigned to the SA group, the NSA group, or the NA group in a 1:1:1 ratio (Fig. 1).

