### Participants

This trial is an exploratory trial which will be conducted in four hospitals in China, including: (I) The Affiliated Hospital of Hebei University of Chinese Medicine; (II) the First Teaching Hospital of Tianjin University of Traditional Chinese Medicine; (III) the Teaching Hospital of Chengdu University of Traditional Chinese Medicine; and (IV) the Affiliated Hospital of Shandong University of Traditional Chinese Medicine. Patients who meet the IBS criteria of Rome IV will be recruited mainly through outpatient clinics, advertisements on hospital social media and newspapers. All patients will receive and fill in the informed consent before randomization.

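### Continuous outcomes are tested with no baseline term, although baseline pain and stool data are collected; this costs precision on secondary outcomes but does not bias them

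*Protocol article*

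**What the plan says.** The Analytical methods section of the protocol article assigns continuous variables to two-sample tests: Student's t "test or Wilcoxon rank-sum test will be used for the comparison of continuous variables". It names no covariate and does not say whether the follow-up value or the change from baseline is compared. The significance rule is P "< 0.05 is considered to indicate statistical significance", with sidedness not given.

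For the primary outcome, a binary response at week 4, the same section does use baseline information: "covariate analysis will be conducted applying a logistic regression model that includes baseline covariates for both pain score and stool consistency".

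The text documents baseline data for pain and stool in four places:
- Inclusion criteria set a floor on mean daily pain in the last week and on loose-stool days in the last 2 weeks.
- Sequence generation requires a 2-week defecation diary before randomization.
- Primary outcome defines response relative to baseline pain and loose-stool days.
- The logistic model needs both values.

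Pain, bloating and stool scores are scheduled at weeks 1, 2, 3, 4, 8 and 12. IBS-SSS, PHQ-9 and IBS-QOL are scheduled at weeks 2, 4, 8 and 12. The text lists no baseline visit for bloating or these three scales. The schedule in Fig. 2 may do so, but it is not reproduced in the text reviewed here.

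On size: "We selected the maximum of 30 patients, and the sample size of 90 patients was determined". This is taken from a regulatory minimum, not from a power calculation.

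**The concern.** With 30 patients per arm, two randomized groups will often differ at baseline by chance. The standard error of a baseline difference is sqrt(2/30) = 0.26 SD, so a gap of more than 0.25 SD arises in about one pairwise comparison in three. A test on follow-up values carries over a share of that gap equal to the baseline-outcome correlation. A test on change scores over-corrects by the remaining share. Neither effect is bias on average over randomizations, but both add noise that a baseline covariate removes.

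The plan already accepts baseline adjustment for a binary outcome built from pain and stool. It then leaves it out for the continuous pain and stool outcomes themselves, where the gain is most direct. At stake are wider confidence intervals than necessary on secondary outcomes, in a pilot meant to inform a larger trial.

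**Working it through.** **Inputs**
- n = 30 per arm, 3 × 30 = 90 in total (Sample size). This reproduces the plan's figure; there is no effect size, SD or power to reproduce.
- Alpha 0.05 (Analytical methods), assumed two-sided; one pairwise comparison.
- Baseline-outcome correlation r: not in the documents, so assumed at 0.3, 0.5 and 0.6.
- True difference of 0.5 SD: assumed, to put power on a common scale.

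**Step 1: the planned test on follow-up values.**
- The 95% CI half-width is t(0.975; 58 df) × sqrt(2/30) = 0.52 SD.
- Power at 0.5 SD, from the noncentral t distribution, is 47.8%.
- The difference detectable with 80% power is 0.74 SD.

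**Step 2: ANCOVA.** The residual variance is the unadjusted variance × (1 − r²), at the cost of 1 degree of freedom. The unadjusted sample size giving the same precision is 30/(1 − r²).

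| r | 1 − r² | Equivalent n per arm | CI half-width (SD) | Detectable at 80% power (SD) | Power at 0.5 SD |
|---|---|---|---|---|---|
| none (planned test) | 1.00 | 30 | 0.52 | 0.74 | 48% |
| 0.3 | 0.91 | 30/0.91 = 33.0 | 0.49 | 0.70 | 51% |
| 0.5 | 0.75 | 30/0.75 = 40.0 | 0.45 | 0.64 | 59% |
| 0.6 | 0.64 | 30/0.64 = 46.9 | 0.41 | 0.59 | 66% |

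A simulation with 10,000 runs gave ANCOVA power of 50.5% at r = 0.3 and 58.7% at r = 0.5, in line with the table.

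**Step 3: if the t test is meant for change scores.** The variance factor becomes 2(1 − r). Since 1 − r² = (1 − r)(1 + r), the ratio of ANCOVA variance to change-score variance is (1 + r)/2, which never exceeds 1.
- At r = 0.3, 0.5 and 0.6 the ratio is 0.65, 0.75 and 0.80.
- Change-score power at 0.5 SD is 36%, 48% and 57%, below ANCOVA each time.

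The conclusion therefore does not depend on which version the plan intends.

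**Step 4: centre.** The trial "will be conducted in four hospitals in China", so a centre factor costs 3 degrees of freedom. With an assumed intraclass correlation of 0, 0.05 or 0.10 and no baseline term, power at 0.5 SD is 47.7%, 49.7% or 51.8%, against 47.8% without centre. The gain is between nothing and about 4 points.

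**The case against.** Two-sample tests are valid in a randomized trial, and these outcomes are secondary in an exploratory pilot with no power target. A condensed article often lists default tests and leaves the model to a fuller plan. The size of the gain rests on a correlation that the documents do not give. The entry floors on pain and loose-stool days restrict the range of exactly the two measures with a documented baseline, which tends to lower that correlation. At r = 0.3 the gain is worth only 3 patients per arm. All of this stands as a limit on importance. It does not remove the point, because the article names the tests and a plan that followed it would carry them forward.

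A reader might infer four stronger claims that the documents do not support:

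- **That the comparisons are biased or the tests invalid.** Randomization protects both; only precision is lost.
- **That every continuous outcome has an unused baseline.** The text shows this only for pain and stool. For IBS-SSS, PHQ-9, IBS-QOL and bloating it depends on Fig. 2.
- **That leaving out centre is a material defect.** The article says only "The block randomization will be used in the trial" and states no stratification by centre, so no stated design feature calls for a centre term. Nor does it say that each hospital has separate acupuncturists. The likely gain is small.
- **That the primary analysis should be re-ranked, or centre added to it.** A baseline-adjusted logistic model is already planned and is nowhere placed below the chi-square test. The 1 − r² calculation applies to linear models; in logistic regression, adjustment changes the odds ratio being estimated. With 2 arm, 2 baseline and 3 centre terms, and an assumed 30% response rate, 27 responders over 7 terms is fewer than 4 per term.

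It is also tempting to argue that the pilot would hand the wrong SD to the next trial. The primary endpoint is a response rate, raw SDs will be reported, and a residual SD can be derived later from the stored data, so that argument adds little.

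**Conclusion.** The point holds as an avoidable loss of precision on continuous secondary outcomes. It is established for pain and stool, and conditional for the other scales on a baseline being collected. Under assumed correlations of 0.3 to 0.6, adjustment removes 9% to 36% of the variance, worth about 3 to 17 extra patients per arm. Power at an assumed 0.5 SD rises from 48% to between 51% and 66%. The gain is modest at 0.3 and material from about 0.5 upwards. The direction does not depend on whether follow-up values or changes are tested, because ANCOVA is at least as precise as the change-score test at every correlation. The primary outcome is not affected.

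**What to change.** In Analytical methods, replace the t test as the main comparison for the abdominal pain and stool outcomes by one of these:
- ANCOVA at each time point, with arm and the outcome's own baseline value; or
- a mixed model for repeated measures with arm, time, arm-by-time and the outcome's own baseline value.

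Apply the same to every other continuous scale whose baseline is confirmed in the Fig. 2 schedule, and state in the outcome text that the baseline is collected. Keep the Wilcoxon rank-sum test as a supportive analysis where distributions are skewed. If the mixed model is chosen, say how it fits with the planned LOCF or multiple imputation for these outcomes.

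Centre may be added as a factor in these linear models, with a small expected gain for 3 degrees of freedom. Leave the logistic model for the primary outcome as it stands on this point.

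The cost is revised wording, standard code and 1 degree of freedom for the baseline term. No extra patients are needed, and no extra visits where the baseline is already collected.
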